#### Statistical analysis and power

2.3.5.

We will first calculate descriptive statistics and generate visual plots to assess the balance of individual-level covariates between intervention and control groups at baseline and to depict informative cross-sectional and longitudinal patterns in the data. For the intervention effects on vascular health and cognitive function, we will analyze the data using group randomized trial methods that account for clustering of individuals within intervention cohorts and appropriately modify the degrees of freedom (Murray et al., 2004). Primary outcomes are blood pressure, hemoglobin A1c, blood lipids, and body-mass-index for vascular risk factors, CCI for subjective memory complaints, QDRS for attention and memory scores for cognitive function, and the Cognivue^®^ for general cognition. CCI and QDRS will be analyzed as continuous and dichotomous variables. QDRS will be dichotomized at the recommended cut-off scores of 2–5.5 for mild and ≥ 6 moderate/severe impairment (Maruff et al., 2013). CCI will use the recommended cut-off scores for SCI as 6 ≤ and less than 6 as normal cognitive function. Secondary outcomes will be other measures of vascular risk factors, cognitive function, and other variables relevant to ADRD risk. Separate regression models will be fit for each of the outcomes with no adjustment for multiple comparisons.

Linear or logistic hierarchical models will be specified to model continuous or binary versions of the outcomes (Table 3), respectively. Normality assumptions will be assessed by Q-Q plots and transformations when appropriate. All models will include a cohort-level random intercept. Analyses will first estimate the effect of the intervention on each of the primary outcomes separately for 3, 8, and 12 months. If doing so improves model fit, we will also fit a model that includes all time points and a cohort-level random slope over time. Time (baseline and 3, 8, and 12-months) will be modeled as a categorical and continuous variable. If the model fit is not significantly different, we will retain the latter as the more parsimonious specification. All models will include a binary indicator for randomization to the immediate intervention arm. We will include a coefficient for the intervention × time interaction to estimate divergence between the 2 study arms during follow-up. This term represents the statistical test of the intervention for improving the outcome. For sensitivity analysis, we will adjust for individual-level covariates for which there is evidence of imbalance between the two study arms at baseline. Lastly, we will conduct exploratory analyses to evaluate potential mediation of the intervention effect by relevant covariates (e.g., better sleep quality as an explanation for improved cognitive function) by including the potential mediators in the model to estimate controlled direct effects of the intervention. Results for inferential analyses will be reported as mean or risk differences and ratios with 95 % confidence intervals.

For GRT, statistical power is a function of the number of groups per study arm as well as the number of participants per group (Murray et al., 2004). We estimated minimum detectable effect sizes for a GRT with 8 groups per condition, 9 participants per group and approximately 80 % retention over 12 months at an alpha = 0.05. We assumed an intra-cohort correlation of 0.01 and a within-person correlation of 0.8 or 0.5 over time. We estimated standard deviations for vascular risk factors based on data from the KāHOLO Project and on previous research for hemoglobin A1c (Sinclair et al., 2013) and cognitive outcomes (Rattanabannakit et al., 2016). Table 3 shows the estimates for 80 % power to detect mean differences in the clinical variables, which depends on correlation over time. For continuous cognitive outcome measures (Cognivue^®^, CCI, NSCT), we have 80 % power to detect a standardized effect size of 0.38–0.56 (for within-person correlation over time of 0.8 or 0.5, respectively). The NIH website estimated power using GRT power calculators (U.S. Department of Health and Human Services, n.d.).

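### The multi-visit models name only cohort-level random effects, so as written they do not match the within-person correlation on which the power statement rests

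*Protocol article*

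**What the plan says.** All of this is in the protocol article, section 2.3.5, unless noted.

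- **Clustering to be handled.** The methods are to "account for clustering of individuals within intervention cohorts and appropriately modify the degrees of freedom". Repeated measurement of the same person is not mentioned there.
- **Random effects.** "All models will include a cohort-level random intercept". If it improves fit, the team will also fit "a model that includes all time points and a cohort-level random slope over time". Both terms are at cohort level.
- **Visits.** "Time (baseline and 3, 8, and 12-months) will be modeled as a categorical and continuous variable". Table 2 shows four visits for the vascular measures. The cognitive measures have three values: screening or baseline, 8 months and 12 months.
- **Test.** Of the intervention-by-time coefficient the article says: "This term represents the statistical test of the intervention for improving the outcome".
- **Order of analysis.** "Analyses will first estimate the effect of the intervention on each of the primary outcomes separately for 3, 8, and 12 months".
- **Power.** "We assumed an intra-cohort correlation of 0.01 and a within-person correlation of 0.8 or 0.5 over time". With 8 cohorts per arm, 9 people per cohort and about 80% retention, the article claims 80% power for 0.38 to 0.56 SD on the continuous cognitive outcomes. Table 3 gives matching differences for the vascular outcomes, such as systolic pressure 5.8 or 8.4 with SD 15 (5.8/15 = 0.387; 8.4/15 = 0.560).

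**The concern.** The intervention-by-time coefficient compares change between arms, so it is a within-person contrast. Its true variance falls as a person's visits become more alike. A model with cohort terms only gives two visits from one person almost no correlation beyond the shared cohort effect (about 0.01). It therefore charges the contrast with the full between-person variance, and the standard error is too large.

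The power paragraph takes credit for the within-person correlation that the named model terms do not use. If the analysis follows the text, effects of the size the trial was planned to detect would usually be missed at correlation 0.8, and missed about half the time at 0.5. This would affect every primary outcome analysed with more than one visit per person.

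**Working it through.** **Inputs.** From section 2.3.5: 8 cohorts per arm, 9 per cohort, 80% retention, so m = 9 × 0.8 = 7.2 per cohort and n = 8 × 7.2 = 57.6 per arm; ICC = 0.01; within-person correlation ρ = 0.8 or 0.5; alpha 0.05. Assumed: two-sided alpha, the same ρ between any two visits, cohort effects uncorrelated over time, outcome SD = 1.

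**Step 1: reproduce the plan's figures.** Variance of the difference in change, with the participant's own level removed:

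Var = 4[(1 − ρ)(1 − ICC) + m·ICC]/n

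- ρ = 0.8: 4(0.198 + 0.072)/57.6 = 0.01875, SE = 0.137. Detectable effect (1.960 + 0.842) × 0.137 = 0.384; stated 0.38.
- ρ = 0.5: 4(0.495 + 0.072)/57.6 = 0.03938, SE = 0.198. Detectable effect 0.556; stated 0.56.

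Power at the stated effects is 79% and 81%. A comparison of follow-up values alone does not depend on ρ. It gives 2.802 × 0.192 = 0.538 for both cases, so it cannot produce two different figures. The power statement needs a model that uses ρ.

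**Step 2: standard error that the named terms would report (baseline and 12 months).**

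- Cohort intercept only: √(4 × 0.99/57.6) = 0.262.
- With a cohort-by-time component at its true size: √(4 × (0.99 + 0.072)/57.6) = 0.272.

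Neither depends on ρ. The true SE is still 0.137 or 0.198. A cohort slope can only add to the reported variance, because variance components are normally held at or above zero.

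**Step 3: power of that test.** Power = Φ[(effect − q × model SE)/true SE], with q = 1.960 (normal) or 2.145 (t, 14 df).

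| Model SE | q | ρ 0.8, effect 0.38 | ρ 0.5, effect 0.56 |
|---|---|---|---|
| 0.262 | 1.960 | 16.4% | 59.2% |
| 0.272 | 1.960 | 13.3% | 55.6% |
| 0.262 | 2.145 | 9.1% | 49.5% |
| 0.272 | 2.145 | 7.0% | 45.5% |

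Type I error is 2Φ(−q × model SE/true SE). The largest values, from the first row, are 0.0002 (ρ = 0.8) and 0.0096 (ρ = 0.5). With normal quantiles and model SE 0.262, the effect needed for 80% power is 1.960 × 0.262 + 0.842 × 0.137 = 0.63 SD, or 0.68 SD with true SE 0.198.

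**Step 4: sensitivity.**

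- Simulation, two visits, 7 per cohort: 19% and 59% with the cohort intercept only; 11% and 49% with a cohort slope and 14 df. Type I error was at most 0.0123.
- Simulation with 9 per cohort (no dropout): 30% and 72%; 19% and 63% with the slope and 14 df.
- Four visits with linear time, normal quantiles: 23% and 68% without a participant term, 85% and 87% with one.

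**Step 5: separate time-point models, one follow-up row per person, no baseline adjustment.** SE = √(2 × (1 + 6.2 × 0.01)/57.6) = 0.192. Power is Φ(0.38/0.192 − 1.960) = 51% and Φ(0.56/0.192 − 1.960) = 83%.

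**Step 6: two-visit model with a participant term.** Power at the stated effects is 79% and 81% with normal quantiles, or 74% and 75% with 14 df.

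**The case against.** The strongest reply is that this is a condensed article. Saying that models will include a cohort intercept sets a minimum and does not rule out other terms. The reference to hierarchical models, and a power calculation built on within-person correlation, suggest that the authors meant to model it. A full analysis plan may say so. This stands in part: a reader might infer that the plan excludes a participant term, and the text does not support that. The term is unnamed, not ruled out. But the article goes beyond leaving the structure open. It gives the level of each random effect it names and the coefficient to be tested, and those do not fit its own power paragraph.

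Second, the separate time-point analyses come first, and the joint model depends on improved fit. With one follow-up row per person those models need no participant term. A reader might therefore infer that no analysis in the plan could reach 80%; that is too strong, since such a model reaches about 83% at 0.56 SD. But it has no intervention-by-time term, so it is not the declared test, and it reaches only about 51% at 0.38 SD. If the separate models instead carry baseline rows and an interaction, they are the two-visit case worked above.

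Third, the error is conservative. That is correct: the declared test does not gain false positives. The cost is lost power.

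Fourth, the size varies with the number of visits, the coding of time, dropout and degrees of freedom. This also stands, so a range is given. None of the variants examined without a participant term brings the interaction test to 80%.

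**Conclusion.** The concern holds as a mismatch between the analysis model as written and the power statement. In the two-visit calculation, power is roughly 7–16% at 0.38 SD (correlation 0.8) and 46–59% at 0.56 SD (correlation 0.5), against the claimed 80%. Type I error is at most about 1% against 5%. The loss is much larger at the higher correlation.

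These figures rest on two-sided alpha, 7.2 retained per cohort, ICC 0.01, equal correlation between visits and cohort effects uncorrelated over time. If cohort effects are instead constant over time, the true SEs become √(4 × 0.2 × 0.99/57.6) = 0.117 and √(4 × 0.5 × 0.99/57.6) = 0.185. Power with model SE 0.262 and normal quantiles is then 13% and 60%, so the conclusion does not turn on that assumption.

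The documents do not show that the final analysis will omit a participant term; they show that the published specification lacks one and cannot support Table 3 or the 0.38–0.56 SD claim without it.

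**What to change.** - In every model with more than one visit per person, add a participant random intercept nested in cohort, or an unstructured within-person covariance over visits. Keep the cohort-level terms and the small-sample degrees of freedom.
- In the separate 3-, 8- and 12-month models, use one follow-up row per person and adjust for the baseline value of the outcome. For the cognitive measures, Table 2 allows this at 8 and 12 months only.
- State how the separate models relate to the intervention-by-time test.
- Restate power for the chosen model. In the two-visit calculation the stated effects have about 74–75% power with 14 df, or 79–81% with normal quantiles.

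The cost is a line or two of model specification and one recalculation. No new data and no change to the design are needed.

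### The intervention × time test can leave out cohort-by-time variation, because the cohort random slope is included only if it improves model fit

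*Protocol article*

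**What the plan says.** All of this is in the Protocol article, section 2.3.5 (Statistical analysis and power).

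- General commitment: group-randomised methods that "account for clustering of individuals within intervention cohorts and appropriately modify the degrees of freedom".
- First step: "Analyses will first estimate the effect of the intervention on each of the primary outcomes separately for 3, 8, and 12 months".
- Cohort term in every model: "All models will include a cohort-level random intercept".
- Cohort slope: "If doing so improves model fit, we will also fit a model that includes all time points and a cohort-level random slope over time". No fit criterion is named.
- Declared test, referring to the intervention × time coefficient: "This term represents the statistical test of the intervention for improving the outcome".
- Power: "8 groups per condition, 9 participants per group", with "approximately 80 % retention over 12 months at an alpha = 0.05", an intra-cohort correlation (ICC) of 0.01 and a within-person correlation of 0.8 or 0.5. The standardised detectable effects are 0.38 and 0.56, and Table 3 gives the vascular outcomes in their own units.

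No participant-level random effect or residual correlation structure is mentioned in the description of the models.

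**The concern.** Cohorts are the randomised units, so the test of a difference in change between arms must be judged against how much cohorts differ in their change. In a linear model a cohort random intercept cannot supply this: it adds the same amount at baseline and at follow-up and drops out of the difference. Only a cohort × time term (a random slope, or a cohort-by-visit effect) brings clustering into the declared test. Clustering that arises after baseline, for example from shared lessons, appears only in that term.

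The plan lets model fit decide whether the term is present. With 16 cohorts a fit check has little power to detect a small between-cohort variance, so failing to find one is weak evidence that it is absent. At stake are the standard error, the confidence interval and the false positive rate for the continuous primary outcomes.

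**Working it through.** **Inputs.** From section 2.3.5: g = 8 cohorts per arm; 9 per cohort × 0.80 retention gives m = 7.2; ICC = 0.01; ρ = 0.8 or 0.5; alpha 0.05; power 80%. Assumed: a two-sided test, and a cohort-level correlation over time rg, which is not stated.

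**Step 1. Reproduce the stated detectable effects.** In SD units the variance of the difference in change is

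V = 4 × [(1 − ICC)(1 − ρ) + m × ICC × (1 − rg)] / (m × g), and the detectable effect is (1.960 + 0.842) × √V.

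With rg = 0:
- ρ = 0.8: V = 4 × (0.198 + 0.072)/57.6 = 0.01875, effect 0.384 (stated 0.38).
- ρ = 0.5: V = 4 × (0.495 + 0.072)/57.6 = 0.03938, effect 0.556 (stated 0.56).
- Systolic pressure, SD 15: 5.75 and 8.34 (Table 3: 5.8 and 8.4). Lipids, SD 35: 13.4 and 19.5 (Table 3: 13.4 and 19.7).

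Alternatives fit less well:
- Without the cohort term (0.072): 0.329 and 0.519.
- Without it but with t quantiles on 14 df (multiplier 3.013 instead of 2.802): 0.353 and 0.559, so only the second figure matches.
- With rg = ρ: 0.340 and 0.538.

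The planned power therefore appears to count cohort variance in change. That variance is 0.072/0.270 = 27% of V at ρ = 0.8 and 0.072/0.567 = 13% at ρ = 0.5.

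**Step 2. Convert the ICC to a share of change variance.** With rg = 0 the between-cohort share is ICC / [ICC + (1 − ICC)(1 − ρ)]:
- ρ = 0.8: 0.01/(0.01 + 0.198) = 4.8%.
- ρ = 0.5: 0.01/(0.01 + 0.495) = 2.0%.

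If rg = ρ, the share is 1% in both cases.

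**Step 3. Simulate trials with no effect.** Setup: 16 cohorts × 7 analysed, personal change as the outcome (so within-person correlation is already handled), 200,000 trials per setting. When the cohort term is dropped, error is pooled on 16 × 7 − 2 = 110 df. When it is kept, the test uses cohort means on 14 df. LRT is the REML likelihood-ratio test.

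| Rule, equal cohort variance in both arms | Share 2.0%: kept / type I error | Share 4.8%: kept / type I error |
|---|---|---|
| Never included, 110 df | – / 6.4% | – / 8.4% |
| Kept by AIC | 12.7% / 5.7% | 24.5% / 6.7% |
| Kept by LRT, cut-off 2.71 | 8.6% / 5.9% | 18.3% / 7.1% |
| Kept by LRT, cut-off 3.84 | 4.8% / 6.1% | 11.6% / 7.6% |
| Kept by BIC | 3.1% / 6.2% | 8.2% / 7.8% |
| Never included, 14 df | – / 4.5% | – / 6.2% |
| Always included, 14 df | – / 5.0% | – / 5.0% |

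With cohort variance in the intervention arm only, the rates are 5.8% and 6.8% if never included on 110 df, 5.3–5.7% and 5.9–6.5% under selection by fit, and 4.1% and 4.8% if never included on 14 df.

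**Step 4. Read the model literally.** With a cohort intercept and no participant-level term, between-person variance stays in the residual of a change contrast. The type I error is then far below nominal, about 0.002% to 1.1%.

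**The case against.** The strongest reply is that the plan never says it will fit an all-visit model without the slope. The sentence ties the two together, so a failed fit check may simply leave the separate analyses at 3, 8 and 12 months. If those use follow-up values only, the cohort intercept does carry clustering into the arm comparison. This stands as a reading of the text. But such models contain no intervention × time term, which is the declared test; if they stack baseline with follow-up so as to contain one, the intercept cancels again. The text does not say which is meant.

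Second, section 2.3.5 promises to modify the degrees of freedom, and the exact method can properly be left to an analysis plan. This also stands in part: 14 df removes the excess at a 2.0% share and most of it at 4.8% (6.2%). It cannot repair a standard error that omits a variance component.

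Third, section 2.1.1 (Rationale) calls the trial partially nested, with no group intervention in the control arm. Clustering from lessons would then arise in 8 cohorts only, and the inflation is smaller, as shown above.

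A reader might infer that the usual result will be a test that ignores the cohorts, has hundreds of degrees of freedom and is clearly anti-conservative. The documents do not support that. No residual degrees of freedom are specified, the fallback model is ambiguous, and with no participant-level correlation the error runs the other way.

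**Conclusion.** The rule should be changed, but the demonstrated inflation is modest and conditional. A term that the declared test needs for valid clustering is left to a fit check that would usually drop it. That is inconsistent with the section's own commitment on clustering and with the variance its power figures appear to include.

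The type I error rates in the working (about 5.5–7% under AIC or the 2.71 cut-off, slightly more under stricter criteria) rest on five assumptions: an all-visit or stacked model without the slope, within-person correlation modelled, residual degrees of freedom, equal cohort variance in both arms, and rg = 0. The last is not stated; it is the value that reproduces the power figures. Relaxing the second makes the test conservative, and relaxing any of the last three lowers the rate. The cancellation argument is for the linear models; the binary versions were not examined.

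**What to change.** In section 2.3.5, replace the fit-dependent sentence with a fixed rule:

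- Any model that tests intervention × time always contains a cohort × time random effect, whatever its estimated size or effect on fit: a random slope if time is continuous, a cohort-by-visit effect if time is categorical.
- The same model handles within-person correlation, and the text says how.
- The test uses cohort-based degrees of freedom: 16 − 2 = 14 before any site or pair terms, kept even if the variance estimate is zero.
- State whether the separate-visit analyses use follow-up values alone or stack baseline with follow-up, and how they relate to the declared test.

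This is wording only and needs no new data. The cost is slightly wider intervals. Replacing the multiplier 2.802 by 3.013 (a factor of 1.075) moves the detectable effects from 0.38 and 0.56 to about 0.41 and 0.60, or from 5.8 and 8.4 to about 6.2 and 9.0 mmHg systolic. If negative variance estimates are set to zero while 14 df are kept, the test is somewhat conservative (3.1% and 3.8% in the two settings above).

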**Other Variables**					
Demographics		X			
Neighborhood factors		X			X
Family History		X			X
Bilingualism		X			
Occupational Scale		X			X

**Table 3 T3:** Power for group-randomized trial vascular outcomes.

Outcome	Minimum detectable difference between treatment arms		SD
	*ρ* _ *m = 0.8* _	*ρ* _ *m = 0.5* _	
Blood lipids	13.4	19.7	35
Hemoglobin A1c	0.8	1.2	2.2
Systolic blood pressure	5.8	8.4	15
Diastolic blood pressure	4.2	6.2	11
Body mass index	3.1	4.5	8

SD = standard deviation; ρ_m_ = *within-person correlation over time*.

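### The first-step visit models name no baseline-outcome covariate, while the declared test sits in a joint model fitted only if fit improves; Table 3 matches only the latter

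*Protocol article*

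**What the plan says.** All statements are in the protocol article, section 2.3.5 (Statistical analysis and power), unless noted.

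- First step: "Analyses will first estimate the effect of the intervention on each of the primary outcomes separately for 3, 8, and 12 months". Every model has a cohort-level random intercept and an indicator for the immediate-intervention arm. No baseline-outcome covariate is named.
- Second step: a model with all time points and a cohort-level random slope is added only if this improves model fit. Baseline is one of the levels of time. The intervention-by-time interaction is declared to be the statistical test of the intervention.
- Covariates: "For sensitivity analysis, we will adjust for individual-level covariates for which there is evidence of imbalance between the two study arms at baseline".
- Power: "We estimated minimum detectable effect sizes for a GRT with 8 groups per condition, 9 participants per group", with "approximately 80 % retention over 12 months". "We assumed an intra-cohort correlation of 0.01 and a within-person correlation of 0.8 or 0.5 over time". "Table 3 shows the estimates for 80 % power to detect mean differences in the clinical variables, which depends on correlation over time".
- Table 3, systolic row (difference at 0.8, difference at 0.5, SD): "Systolic blood pressure 5.8 8.4 15".
- Section 2.3.3 calls 12 months the primary endpoint. It also says that the cognitive screening scores serve as baseline, so by Table 2 a baseline value exists for every primary outcome.

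**The concern.** The section describes two analyses that do not fit together. A model for a single follow-up visit has no time term, so the declared intervention-by-time test cannot be carried out in the first-step models. It can be carried out only in the joint model, and whether that model is fitted depends on the data. As written, it is therefore unsettled whether the baseline value enters the intervention estimate.

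This matters for two reasons. First, Table 3 depends on the within-person correlation, and a comparison of follow-up values alone does not use it. Second, in such a comparison a chance baseline difference between arms, multiplied by the within-person correlation, carries into the estimate.

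The covariate rule does not repair this. Under randomisation, an observed imbalance is chance. Choosing covariates by imbalance makes the model data-driven and ignores whether a covariate predicts the outcome. It also operates only in a sensitivity analysis.

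**Working it through.** **Inputs (section 2.3.5 and Table 3).** g = 8 cohorts per arm; 9 people per cohort with about 80% retained, so m = 9 × 0.8 = 7.2 (7 if rounded down); intra-cohort correlation (ICC) 0.01; within-person correlation ρ = 0.8 or 0.5; alpha 0.05; power 80%; systolic SD 15. Sidedness is not stated; two-sided is assumed.

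**Multipliers.** Normal: 1.960 + 0.842 = 2.802. With t on 14 df (16 cohorts minus 2): 3.013.

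**Step 1. Reproduce Table 3 as change from baseline (arm × time).**

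SE in SD units = √{2[2(1−ICC)(1−ρ) + 2m·ICC]/(g·m)}

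- m = 7, ρ = 0.8: √{2(0.396 + 0.14)/56} = 0.1384; × 2.802 × 15 = 5.81 mmHg (stated 5.8)
- m = 7, ρ = 0.5: √{2(0.99 + 0.14)/56} = 0.2009; × 2.802 × 15 = 8.44 mmHg (stated 8.4)
- m = 7.2: 5.75 and 8.34 mmHg
- Standardised: 0.384-0.388 and 0.556-0.563 (stated 0.38 and 0.56)

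The lipid, diastolic and BMI rows agree within 1.5%; HbA1c agrees up to one-decimal rounding. So Table 3 is a change contrast with normal quantiles.

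**Step 2. Follow-up value only, no baseline.**

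SE = √{2[(1−ICC) + m·ICC]/(g·m)}. There is no ρ in it, so it cannot produce two columns.

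- m = 7: √{2(0.99 + 0.07)/56} = 0.1946; × 2.802 × 15 = 8.18 mmHg
- m = 7.2: √{2(0.99 + 0.072)/57.6} = 0.1920; × 2.802 × 15 = 8.07 mmHg

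Power for 5.8 mmHg: Φ(0.3867/0.1946 − 1.96) = 51% at m = 7, and 52% at m = 7.2. Power for 8.4 mmHg: 82-83%.

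**Step 3. Follow-up value with baseline as covariate.** The cohort component is left unreduced, which is conservative.

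SE = √{2[(1−ICC)(1−ρ²) + m·ICC]/(g·m)}

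- m = 7, ρ = 0.8: √{2(0.3564 + 0.07)/56} = 0.1234; 5.19 mmHg
- m = 7, ρ = 0.5: √{2(0.7425 + 0.07)/56} = 0.1703; 7.16 mmHg
- m = 7.2: 5.13 and 7.07 mmHg

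Power at Table 3's own differences: 88-89% (ρ = 0.8) and 91% (ρ = 0.5).

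**Summary: detectable systolic difference at 80% power, mmHg, over m = 7 to 7.2.**

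| Analysis | ρ = 0.8, normal | ρ = 0.5, normal | ρ = 0.8, t(14) | ρ = 0.5, t(14) |
|---|---|---|---|---|
| Change from baseline (Table 3) | 5.8 | 8.3-8.4 | 6.2-6.3 | 9.0-9.1 |
| Follow-up only | 8.1-8.2 | 8.1-8.2 | 8.7-8.8 | 8.7-8.8 |
| Baseline as covariate | 5.1-5.2 | 7.1-7.2 | 5.5-5.6 | 7.6-7.7 |

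With t on 14 df, follow-up-only power for 5.8 mmHg is 46-47%.

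**Step 4. Size of a chance baseline difference.** With 72 per arm and ICC 0.01, the design effect is 1 + 8 × 0.01 = 1.08. The SE of the baseline systolic difference is 15 × √(2 × 1.08/72) = 2.6 mmHg. Individual randomisation of 144 people would give 15 × √(2/72) = 2.5 mmHg.

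**The case against.** The strongest reply is that the section does use baseline. It makes baseline a level of time and names intervention by time as the test. That is a change contrast, and Table 3 reproduces as exactly that. The separate-visit estimates might themselves be meant as baseline-to-visit contrasts, and a condensed article may leave model detail to a fuller plan.

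Much of this stands, and it rules out several stronger readings:

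- A reader might infer that the trial discards the within-person correlation altogether. The documents do not support that. It is true only of the separate-visit models taken literally.
- A reader might infer a power loss at both correlations. On the normal basis behind Table 3, follow-up-only does slightly better than the change contrast at ρ = 0.5. An apparent loss there arises only if t-based figures are set against normal-based ones.
- A reader might think that randomising 16 cohorts makes serious baseline imbalance especially likely. At the assumed ICC, the chance difference is barely larger than under individual randomisation (2.6 against 2.5 mmHg).
- Only cohort-level random effects are named, so a reader might infer that repeated measures on one person will be treated as independent. The article does not say so, and the person-level covariance may be set out elsewhere.

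What the reply does not remove: the article does list model terms, does fix an order of analysis, and does fix a covariate rule. The declared test has no place in a single-visit model, and the model that contains it depends on fit. Even a firmly specified change contrast is less precise than baseline adjustment at both correlations.

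**Conclusion.** The point holds as an inconsistency of specification with an avoidable loss of precision. The first-step models and the declared test are different analyses, and Table 3 belongs to the second, which is conditional on fit.

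If the separate-visit models are run literally on follow-up values, the detectable systolic difference at ρ = 0.8 is about 40% larger than stated (8.1-8.2 against 5.8 mmHg), with power of 51-52% for 5.8 mmHg (46-47% with t on 14 df). At ρ = 0.5 there is no loss on the normal basis. Using baseline as a covariate improves on Table 3's contrast at both correlations.

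These figures rest on the plan's ICC of 0.01, 7 to 7.2 people analysed per cohort, two-sided alpha 0.05, equal cohort components in both arms, and no reduction of the cohort component by the baseline covariate. The imbalance-triggered covariate rule is poor practice in its own right, but it affects only a sensitivity analysis. The plan should be changed; the design need not be.

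**What to change.** 1. Name one primary model per outcome at 12 months, used whether or not a joint model improves fit. Either form will do:
   - the 12-month value with the baseline value of the same outcome as a prespecified covariate; or
   - a repeated-measures model with baseline in the response, person-level correlation, and arm means constrained equal at baseline.

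   Keep the cohort random intercept and the modified degrees of freedom in either case. Apply the same use of baseline to the 3- and 8-month estimates.
2. Replace imbalance-triggered selection with a few prespecified individual-level prognostic covariates, for example age and SCI/MCI status.
3. Recompute Table 3 for the chosen model, and state whether normal or t quantiles are used.

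The cost is wording and one recalculation. No new data are needed, and individual-level covariates use essentially no cohort-level degrees of freedom. Site adjustment is optional and is not free: site is a cohort-level factor, and five organisations would take 4 of the 14 degrees of freedom.
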